## Abstract

**Background:**

Borderline personality disorder (BPD) is associated with a high socioeconomic burden. Although a number of evidence-based treatments for BPD are currently available, they are not widely disseminated; furthermore, there is a need for more research concerning their efficacy and cost-effectiveness. Such knowledge promises to lead to more efficient use of resources, which will facilitate the effective dissemination of these costly treatments. This study focuses on the efficacy and cost-effectiveness of Mentalization-Based Treatment (MBT), a manualized treatment for patients with BPD. Studies to date have either investigated MBT in a day hospitalization setting (MBT-DH) or MBT offered in an intensive outpatient setting (MBT-IOP). No trial has compared the efficacy and cost-effectiveness of these MBT programmes. As both interventions differ considerably in terms of intensity of treatment, and thus potentially in terms of efficacy and cost-effectiveness, there is a need for comparative trials. This study therefore sets out to investigate the efficacy and cost-effectiveness of MBT-DH versus MBT-IOP in patients with BPD. A secondary aim is to investigate the association between baseline measures and outcome, which might improve treatment selection and thus optimize efficacy and cost-effectiveness.

**Methods/Design:**

A multicentre randomized controlled trial comparing MBT-DH versus MBT-IOP in severe BPD patients. Patients are screened for BPD using the Structured Clinical Interview for DSM-IV Axis II Personality Disorders, and are assessed before randomization, at the start of treatment and 6, 12, 18, 24, 30 and 36 months after the start of treatment. Patients who refuse to participate will be offered care as usual in the same treatment centre. The primary outcome measure is symptom severity as measured by the Brief Symptom Inventory. Secondary outcome measures include parasuicidal behaviour, depression, substance use, social, interpersonal, and personality functioning, attachment, mentalizing capacities, and quality of life. All analyses will be conducted based on the intention-to-treat principle. Cost-effectiveness will be calculated based on costs per quality-adjusted life-year.

**Discussion:**

This multisite randomized trial will provide data to refine criteria for treatment selection for severe BPD patients and promises to optimize (cost-)effectiveness of the treatment of BPD patients.

**Trial registration:**

NTR2292. Registered 16 April 2010.

## Background

Borderline personality disorder (BPD) is among the most prevalent mental disorders [1,2]. The inability to mentalize, particularly in emotional interactions, is considered to be one of the key problems in BPD [3]. Mentalizing refers to “the mental process by which an individual implicitly and explicitly interprets the actions of himself and others as meaningful on the basis of intentional mental states such as personal desires, needs, feelings, beliefs, and reasons” ([3], p21). Patients with BPD typically suffer from severe impairments in this capacity, resulting in emotional instability, impulsive behaviour, and vulnerability in interpersonal and social interactions [3]. Severe BPD patients almost invariably show high psychiatric comorbidity, particularly depression, anxiety or eating disorders, substance abuse [4-6], various other personality disorders [4,7-12] and high levels of acting-out (e.g., suicidality) [13]. BPD is also associated with seriously impaired quality of life [1] and a high economic burden of disease [14]. Lifetime risk for completed suicide associated with BPD is up to 10% [13]. Together, these findings emphasize the need for the development and dissemination of effective treatments for this severe disorder.

Psychotherapy is considered to be the treatment of choice for BPD patients [1,2]. Several guidelines [2,15-19] recommend outpatient psychotherapy such as Transference Focused Psychotherapy [20,21], Dialectical Behaviour Therapy [22], Schema-Focused Therapy [23], and Mentalization-Based Treatment (MBT) [3] for BPD.

This study focuses on MBT. MBT, which was developed by Bateman and Fonagy [3,24,25] in the United Kingdom, is a promising evidence-based treatment that has its roots in attachment theory. The aim of MBT is to help patients develop an increasingly robust mentalizing process within everyday interpersonal interactions. A day hospital MBT (MBT-DH) [26-28] and an intensive outpatient MBT (MBT-IOP) [29] programme have been developed and empirically evaluated. Although the programmes are similar in length (18 months, consisting of a 12 month treatment and 6 months maintenance phase), they differ markedly in intensity, particularly with regard to the role of group therapy. The treatment phase of MBT-DH consists of a five days per week day hospital treatment that comprises daily group psychotherapy, weekly individual psychotherapy, individual crisis management from a mentalizing perspective, art therapy twice a week, mentalizing cognitive therapy, and writing therapy. MBT-IOP consists of group psychotherapy once a week, weekly individual psychotherapy, and individual crisis management from a mentalizing perspective.

Both treatment programmes have been empirically evaluated in randomized controlled trials (RCTs), but none of these trials has directly compared MBT-IOP and MBT-DH. In a first trial [26-28], 38 BPD patients were randomized to either MBT-DH or treatment as usual (TAU). TAU consisted of standard treatment offered in the UK in general psychiatric services and consisted of (a) regular psychiatric review with a senior psychiatrist when necessary (on average twice a month), (b) inpatient admission when necessary, with discharge to nonpsychoanalytic psychiatric partial hospitalization focusing on problem solving, followed by (c) outpatient and community follow-up as standard aftercare [26]. Results after 18 months showed that MBT-DH was superior to TAU on all major outcome variables; that is, depressive symptoms, suicide attempts and self-harm, number of inpatient days, and social and interpersonal functioning. These results were maintained during an additional 18-month follow-up period [30]. At 5-year follow-up after discharge, the MBT-DH group showed further improvements on suicidality, diagnostic status, service use, use of medication, global functioning scores above 60 (Global Assessment of Functional Scale; GAF) and vocational status [28]. For example, whereas 74% of the patients in the TAU condition made at least one suicide attempt, only 23% in the MBT-DH group did so. At the end of the follow-up period, 13% of the MBT-DH patients met diagnostic criteria for BPD, compared with 87% of the TAU group. This trial also yielded data concerning health costs. Before treatment, the total health-related costs for the MBT-DH group ($44,947) and the TAU group ($52,563) were comparable; after 18 months of treatment, costs were reduced to $27,303 in MBT-DH and $30,976 in TAU. During the 18-month follow-up, costs further diminished sharply in the MBT group. At 18-month follow-up, the total health-related costs in the MBT-DH group were one-fifth of costs for patients in the TAU condition ($3,183 for MBT-DH versus $15,490 for TAU) [30]. However, this study did not include a formal cost-effectiveness analysis.

Two other studies provide further support for the efficacy of MBT-DH. An RCT in Denmark investigated the efficacy of MBT-DH compared with a less intensive manualized supportive group therapy combined with psychoeducation and medication treatment in patients diagnosed with BPD [31]. In total, 58 patients were randomly allocated to MBT-DH and 27 patients to the specialist combined treatment. Results showed that both MBT-DH and the less intensive supportive group therapy led to significant improvements on a variety of psychological and interpersonal measures, e.g., general functioning, depression, social functioning and number of diagnostic criteria for BPD [32], with moderate to large effect sizes (*d* = 0.5 to 2.1). MBT-DH was superior only on therapist-rated GAF [31] after two years of treatment. No follow-up or cost-effectiveness data are yet available from this trial. A naturalistic effectiveness study in the Netherlands [33] investigated the effectiveness of 18-month, manualized MBT-DH in 45 patients with severe BPD and high comorbidity in terms of Axis I and Axis II disorders. Results showed significant improvements in symptomatic distress, social and interpersonal functioning, and personality pathology and functioning; with moderate to large effect sizes (*d* = 0.7 to 1.7). In addition, the Netherlands study showed that care consumption reduced significantly during and after treatment. However, the lack of a control group limits the ability to draw conclusions about the effectiveness of MBT-DH.

Finally, with regard to MBT-IOP, an RCT [29] showed that this less intensive treatment programme was more effective than structured clinical management in an RCT with 134 BPD patients. Substantial improvements were observed in both treatment conditions across all outcome variables. However, the MBT-IOP group showed a steeper decline on both self-reported and clinically significant problems, including suicide attempts and hospitalization. Cost analyses were not included in this trial.

As noted, a ‘head to head’ cost-effectiveness trial directly comparing MBT-IOP with MBT-DH has not yet been conducted. An indirect comparison between MBT-DH and MBT-IOP based on the UK trials [26,29] is hampered by pretreatment patient differences; with the patients in the MBT-DH trial evidencing substantially higher levels of symptomatic distress, depression and interpersonal problems (between-group difference *d* = 0.7 to 0.8). This stresses the need for a comparative trial that also compares the cost-effectiveness of MBT-DH and MBT-IOP, particularly as MBT-DH may be approximately twice as expensive as MBT-IOP [34].

A further reason why a direct comparison trial is currently indicated relates to the current shift in psychotherapy research from the identification of effective treatments to the search for variables that might predict treatment response, with the hope of better matching patients to specific treatments (i.e., to identify “what works for whom”) [35]. Various patient characteristics have been proposed and studied as predictors of treatment outcome with MBT. Furthermore, changes in mentalizing capacities and attachment have been proposed as mechanisms of change in MBT. Little is known, however, about predictors of treatment and mechanisms of change in the treatment of BPD patients, and with MBT in particular. Bateman and Fonagy [36] found pretreatment severity, defined in terms of the number of personality disorders, to be a possible indicator for more favorable treatment outcomes in specialist treatment. No study to date has investigated purported mechanisms of change in MBT. The current trial therefore aims to identify potential predictors of response in both treatments with the aim to facilitate treatment selection and optimize (cost)-effectiveness. Furthermore, it aims to investigate mechanisms of change in both treatment programmes.

### Research aims and hypotheses

The primary aim of the present study is to investigate the efficacy of MBT-DH in comparison to MBT-IOP. The primary outcome measure is symptom severity as measured by the Brief Symptom Inventory [37,38]. Secondary outcome measures include parasuicidal behaviour, depression, substance use, social, interpersonal and personality functioning, attachment, mentalizing capacities, and quality of life. We expect that patients in both MBT-DH and MBT-IOP will improve, but that MBT-DH will outperform MBT-IOP because of its higher dosage.

A secondary aim is to investigate the cost-effectiveness of both treatments based on costs per quality-adjusted life-year (QALY). We expect that the greater benefits of MBT-DH will not outweigh the lower costs of MBT-IOP. Therefore, we expect MBT-IOP to be more cost-effective than MBT-DH.

Third, we aim to explore the role of pretreatment variables in predicting treatment outcome in both interventions, with the aim to optimize treatment selection and thus (cost-)effectiveness.

Finally, this study aims to investigate whether MBT is associated with changes in mentalizing capacities and attachment and whether such changes predict treatment outcome.

## Methods/design

### Design

This study is a multisite RCT comparing the efficacy and cost-effectiveness of MBT-DH versus MBT-IOP in the treatment of BPD (see Figure 1). Patients are randomly allocated to either MBT-DH or MBT-IOP and assessed before randomization, before start of treatment and subsequently every 6 months up to 36 months after start of treatment.

**Figure 1 Fig1:**
[figure not shown]
**Patient flow chart.**

Initially, five mental health care centres specializing in the treatment of BPD agreed to participate in this study (NPI, Amsterdam; GGZinGeest, Amsterdam; De Viersprong, location Bergen op Zoom; De Viersprong, location Amsterdam; and Lentis, Groningen). NPI, GGZinGeest, and De Viersprong location Bergen op Zoom all agreed to provide two MBT-DH and two MBT-IOP groups. De Viersprong location Amsterdam and Lentis both agreed to provide one MBT-DH group and one MBT-IOP group. Before the actual start of the study, one of the participating centres (GGZinGeest) could no longer offer MBT-DH because of a reorganization of its clinical services, and accordingly withdrew from participating in the study. Due to implementation problems, NPI reduced its capacity to one MBT-IOP group and one MBT-DH group. De Viersprong location Amsterdam, however, has been able to expand its capacity to two MBT-DH groups and two MBT-IOP groups. Overall, NPI, De Viersprong (locations Bergen op Zoom and Amsterdam) and Lentis will provide a total of 6 MBT-DH and 6 MBT-IOP groups. The recruitment of patients began in January 2012 and ended in June 2014.

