#### Pretreatment

Patients enter the pretreatment programme until a place becomes available in the treatment to which each patient has been randomized (MBT-DH or MBT-IOP). For both MBT-DH and MBT-IOP the pretreatment programme focuses on engaging the patients in treatment and crisis management. It consists of an introductory course to MBT (MBT-I), and biweekly individual sessions with crisis planning as focus. MBT-I is an explicit mentalizing group with a psychoeducational element, which is considered an important part of the programme. The programme consists of 12 highly structured sessions that stimulate patients to consider the overall process of mentalizing and its relation to their problems, and how these problems will be addressed in MBT [25,42].

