#### Main treatment

##### MBT-DH

MBT-DH is an intensive, manualized treatment for patients with BPD. It has been described in detail elsewhere [3,33]. Briefly, MBT-DH consists of a highly structured day hospitalization programme with a maximum duration of 18 months, covering five days per week. MBT-DH consists of the following components: daily group psychotherapy, weekly sessions of individual psychotherapy, individual crisis planning on indication (average: weekly for 3 months and from then on lower in frequency), art therapy twice a week, mentalizing cognitive group therapy, and writing therapy. Each week’s programme is ended with a social hour and a community meeting. Patients in the MBT-DH programme can also consult a psychiatrist upon request and medication is prescribed following American Psychiatric Association (APA) guidelines [15].

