##### MBT-IOP

The main treatment phase in MBT-IOP consists of group psychotherapy twice a week, weekly sessions of individual psychotherapy, and individual crisis management on indication (average: weekly for 3 months and from then on lower in frequency). Patients can also consult a psychiatrist upon request and medication is prescribed following APA guidelines.

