### Sample size and power calculation

Sample size calculation is based on the BSI, the primary clinical outcome variable in this study. We applied the mixed model ANOVA procedure described by Aberson [81], power of 0.80 and a two-sided alpha of 0.05.

We anticipated a medium-sized difference in effect size between MBT-IOP and MBT-DH based on prior research. In their RCT comparing MBT-IOP with structured clinical management, Bateman and Fonagy reported a within-group effect size for MBT-IOP of *d* =1.31 [29]. In their RCT comparing MBT-DH with usual care, the same authors reported a within-group effect size of *d* = 2.30 for MBT-DH at follow-up [26]. Hence, using an indirect comparison, the previous studies suggest at least a medium-size difference in effect (*d* = 0.50) between both treatment programmes. Applying seven repeated measures with a linear decrease of 0.5 SD more in MBT-DH than in the MBT-IOP group and an autoregressive intercorrelation structure with *r* = 0.50 between baseline and the last follow-up, 45 cases are needed in each group.

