### Statistical analyses

First, to investigate potential differences between the two groups at baseline, we will use parametric and nonparametric descriptive statistics, as appropriate. For the main analyses concentrating on primary and secondary outcomes, linear growth curve models for normally distributed outcome measurements will be used, logistic regression for binary data, and Poisson regression models for ordinal data. Results will be expressed in terms of comparison of the slopes for interval data, odds ratios for binary data, and incidence rate ratios for ordinal data. Furthermore, we will perform explorative analyses regarding predictors of differential treatment outcome. All analyses will be conducted according to intention-to-treat principles.

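### The 45 per arm makes no allowance for correlation within the 6 therapy groups per arm, and the named analysis model has no therapy-group term

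*Protocol article*

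**What the plan says.** The Design section (text after Figure 1) says that the remaining locations "will provide a total of 6 MBT-DH and 6 MBT-IOP groups". By location this is 1 + 2 + 2 + 1 = 6 per arm, with equal numbers of both programmes at each location.

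Both programmes are built on group work. The MBT-DH section lists "daily group psychotherapy, weekly sessions of individual psychotherapy" along with further group elements, and the MBT-IOP section lists "group psychotherapy twice a week, weekly sessions of individual psychotherapy". (The Background gives a lower weekly frequency for MBT-IOP group sessions. Those two places need reconciling, but group therapy is a core component on either figure.) Group membership appears to be rolling: "Patients enter the pretreatment programme until a place becomes available in the treatment".

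Under Sample size and power calculation the article says "We applied the mixed model ANOVA procedure", with "power of 0.80 and a two-sided alpha of 0.05". The other inputs are seven measures, a 0.5 SD difference in linear decrease and a within-patient correlation of 0.50. The result is that "45 cases are needed in each group". No ICC, design effect or therapy-group size appears.

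Under Statistical analyses, "linear growth curve models for normally distributed outcome measurements will be used", with slopes compared between arms. No therapy-group, therapist or site term is named, and none is ruled out.

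**The concern.** Patients who share a therapy group and its therapists share part of what determines their outcome. Randomising individuals does not remove this correlation, because it arises after allocation, through the treatment. It adds variance to the difference between arms that a patient-level calculation does not see.

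The two consequences are alternatives. If the analysis ignores groups, standard errors are too small and the type I error exceeds 5%. If it models groups, the type I error is protected but power falls below the stated 80%. Both matter here: the Discussion considers that the programmes may prove equally effective, in which case resources should go to the cheaper one. Overstated precision or overstated power would mislead that decision.

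**Working it through.** **Inputs from the article.** 6 groups per arm; 45 patients per arm; two-sided alpha 0.05; power 0.80.

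**Assumed.** The ICC of the tested quantity (slope or change) between therapy groups, taken as 0.02, 0.05 and 0.10, with equal group sizes.

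**The plan's own figure.** The 45 was not reproduced exactly. For a 0.5 SD difference at the last of seven measures, 80% power and two-sided 5%:

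- Slope comparison, autoregressive correlation falling to 0.5, common baseline: 48 per arm.
- Slope comparison, constant correlation of 0.5: 42 per arm.
- Other variants lay further away.

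The cited procedure is not fully specified and 45 lies between these two, so it is not called wrong. Every variant tried treats patients as independent, and no variant needs a clustering input. The stated 80% is taken as given below.

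**Formulas.**

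- Patients per group: m = 45/6 = 7.5.
- Design effect: DE = 1 + (m − 1) × ICC = 1 + 6.5 × ICC.
- Effective n per arm: 45/DE.
- Type I error if groups are ignored: 2 × [1 − Φ(1.96/√DE)].
- Power if groups are modelled, normal approximation: Φ(2.80/√DE − 1.96), where 2.80 = 1.96 + 0.84.
- Power with a t reference: noncentral t with noncentrality 2.80/√DE on 12 groups − 4 site parameters − 1 arm parameter = 7 df.

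| ICC (assumed) | DE | Effective n per arm | Type I error, groups ignored | Power, groups modelled (normal) | Power, groups modelled (t, 7 df) |
|---|---|---|---|---|---|
| 0 | 1.00 | 45 | 5.0% | 80% | 67% |
| 0.02 | 1.13 | 40 | 6.5% | 75% | 62% |
| 0.05 | 1.33 | 34 | 8.9% | 68% | 55% |
| 0.10 | 1.65 | 27 | 12.7% | 59% | 47% |

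Worked line for ICC 0.05: DE = 1 + 6.5 × 0.05 = 1.325; √DE = 1.151; 1.96/1.151 = 1.703, two-sided tail 8.9%; 2.80/1.151 − 1.96 = 0.47, Φ = 68%.

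A simulation of 40,000 trials per ICC, with 6 groups of 7 or 8 per arm and an analysis that ignores groups, gave the same type I errors: 6.5%, 8.9% and 12.7%.

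**The two harms do not add up.** If groups are ignored, power is Φ(0.84/√DE), about 79%, 77% and 74%. The larger power loss in the table belongs only to an analysis that models groups, and that analysis has no inflated type I error.

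**What would restore an effective 45 with 6 groups.** n = 45 × (1 − ICC)/(1 − 7.5 × ICC) gives 52, 69 and 162 per arm. No number suffices once the ICC reaches 6/45 = 0.133.

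**The case against.** The strongest reply is that this is a condensed article. Its analysis section names a family of models, and a growth curve model can carry a therapy-group level that a statistical analysis plan, not shown here, may specify. This stands. A reader might infer that the analysis treats patients as independent and that the type I error will exceed 5%; the article does not say so. The reply does not reach the sample size, which is set out with its inputs and has no clustering term. Recruitment ended in June 2014, so no later document can add patients to it.

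Four further points limit the concern.

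- **The ICC is assumed.** At 0 there is no inflation, and at 0.01 the type I error is just under 6%.
- **Site is not a cause of inflation.** Every location runs equal numbers of both programmes and patients are randomised individually, so variation between sites largely cancels in the comparison of arms. Omitting site tends to make standard errors too large. Only variation between groups within site and arm, or between their therapists, does the damage.
- **The trial is not simply 6 units against 6.** A reader might infer that from the group count. But patients enter as places open, over 30 months of recruitment, and weekly individual therapy and tailored follow-up are not delivered in groups. Changing membership blurs the clusters and may lower the ICC.
- **Modelling groups has its own cost.** On 7 degrees of freedom, power is about 67% even at an ICC of 0.

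These points narrow the claim. They do not supply the missing allowance.

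**Conclusion.** The concern holds in a conditional form. The calculation of 45 per arm leaves out within-group correlation in a trial whose treatments are delivered in 6 groups per arm, and the published analysis names no term that would capture it. At any positive ICC, the stated alpha and power cannot both be kept at 45 per arm.

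Over assumed ICCs of 0.02 to 0.10, the price is either a type I error of 6.5% to 12.7% or power of 75% to 59% by normal approximation (62% to 47% on 7 degrees of freedom). The size rests on the assumed ICC, on 7.5 patients per group with stable membership, and on taking the stated 80% at face value. The 7-df figures are the cautious end: when the estimated group variance is small, degrees-of-freedom approximations may give more. The article does not support saying that inflation will occur, that site effects cause it, or that both harms occur together.

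**What to change.** - **Primary and secondary models.** Include a random therapy-group effect, on the time slope where it can be estimated, since slopes are what is compared. Include site as a fixed effect, for precision. Use a small-sample correction such as Kenward-Roger or Satterthwaite; about 7 between-group degrees of freedom remain (12 − 4 − 1).
- **Reporting.** Give the estimated ICC with the primary result. Beside the 45 per arm, restate the power over a range of ICC, for example 0 to 0.10.
- **Economic analysis.** Keep group-level bootstrap resampling as a sensitivity analysis only. With 6 clusters per arm it understates the standard error itself, by a factor of about √(5/6) = 0.91.

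The cost is analysis wording, plus therapy-group membership, which treatment records should provide. No new patients and no change in care are needed. Intervals will be wider: the 7-df critical value of 2.36 against 1.96 alone adds about 21%, before any clustering. A random slope may be poorly estimated from 12 groups, so a fallback to a simpler group effect should be fixed before the data are analysed. The stated power will look less favourable.
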